### Measures

#### Therapist workshop measures

Therapist negative Beliefs about Exposure Scale [TBES; (23)]. The TBES assesses the extent to which therapists endorse 21 negative beliefs about exposure therapy. Participants use a 5-point scale (0 = “disagree strongly” to 4 = “agree strongly”) to indicate the extent to which they agree with such items as “most clients have difficulty tolerating the distress exposure therapy evokes.” The TBES is the primary outcome measure for assessing target engagement. Evidence Based Practice Attitudes Scale [EBPAS; (52)]. This is a brief (15-item) measure that assesses four general attitudes toward adoption of EBPs, including such items as “research based treatments are not clinically useful.” This measure will be used to demonstrate the specificity of target engagement with the E2E approach. Specificity is exhibited by the extent to which the training groups differ on belief change while remaining equivalent in attitudes about EBP in general. Exposure Knowledge (36). We have condensed the original 49 multi-choice item measure by selecting 12 multiple-choice items that best fit the didactic content of our training, for instance, “Why is it important to block avoidance during exposure tasks?” Exposure Self-Efficacy (36). This is a 27-item measure of therapists’ confidence in delivering exposure therapy. All items began with “I feel confident in my ability to,” and an example item is “Conduct imaginal exposure.” Items are rated on a 5-point Likert scale ranging from 1 (not confident) to 5 (very confident). This measure has demonstrated high internal consistency and predictive validity in determining the frequency of self-reported clinical use of exposure therapy. Beliefs about Exposure Scale-Training (BES-T). This is a beliefs process measure designed for this study to measure belief change during training activities. The scale consists of six items that assess therapists’ reservations about the safety and tolerability of exposure therapy. The first five items are rated on a 0 (“Completely Disagree”) to 100 (“Completely Agree”) scale and assess perceptions of safety and tolerability of exposure for their patients as well as themselves. The sixth item stated, “I feel very confident in my ability to deliver exposure therapy and I am committed to using it with my anxious clients,” and the response options were either “Not Yet” or “No more practice – I am ready.” Therapists continued with experiential tasks until they endorsed the “I am ready” item. This item is a go/no-go item intended to solicit self-perceptions of whether therapists felt ready and able to use exposure therapy patients with anxiety. Training Acceptability Rating Scale [TARS; (53)]. The TARS is a measure of therapists’ satisfaction with trainings that has good psychometric properties. Participants rate training acceptability and perceived utility on Likert scales (total scores = 6–63), in addition to qualitative feedback.

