**Methods:**

The study will take place in two phases. First, is a case-series analysis to fine-tune training procedures that is already complete, and the second is an ongoing randomized trial that tests the novel exposure to exposure (E2E) training condition against a passive didactic approach. A precision implementation framework will be applied to evaluate the mechanism(s) by which training influences aspects of therapist delivery following training.

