**Figure 3 fig3:**
[figure not shown]
Training activities, hypotheses, and measurement strategy. EBPAS = Evidence Based Practice Attitudes Scale; TBES = Therapist negative Beliefs about Exposure.

**Table 1 tab1:** Measurement strategy and timepoints.

Measure (*Objective*)	Timepoint					
	Baseline	End of core didactics	During experiential (E2E only)	End of workshop	Consult	End of study
TBES (*Primary target*)	X	X		X		X
EBPAS (*Target specificity*)	X	X		X		X
Knowledge (*Candidate target*)	X	X		X		X
Self-efficacy (*Candidate target*)	X	X		X		X
BES-T (*Target process*)			X			
Training satisfaction (*QI*)				X		X
EPCS (*Outcome*)					X	

BES-T = Beliefs about Exposure Scale – Training; EBPAS = Evidence Based Practice Attitudes Scale; EPCS = Exposure Process Coding System; Knowledge = Exposure Knowledge Measure; Self-Efficacy = Measure of Exposure Delivery Self-efficacy; TBES = Therapist negative Beliefs about Exposure; Training Satisfaction = Training Acceptability Rating Scale (TARS).

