##### Exposure to exposure (E2E) condition

Those in the E2E training condition briefly reviewed previous didactic content (1 h), before engaging in experiential training strategies. Experiential activities followed the steps of (1) generating a fear hierarchy, (2) selecting and titrating appropriate exposure tasks, (3) conducting exposure in a prolonged and intense manner, and (4) consolidating learning as described in the “Optimizing E2E” section above. After completing two rounds of self-exposure all therapists completed the BES-T. Regardless of whether they selected “No More Practice – I am Ready” on the BES-T go/no-go item, all therapists then completed two rounds of partner exposures. After two rounds of partner exposures they again completed the BES-T, and those who endorsed “No More Practice – I am Ready” were placed in a waiting room to discuss their current patient caseload and think about potential patient referrals to the study, while those endorsing “Not Yet” completed another round of partner exposure with a study confederate (research assistant) in either the patient or provider role depending on which they thought would be most helpful for increasing their exposure confidence; in all instances, those requiring additional practice elected to be in the therapist role. Therapists repeated the partner exposure task and completed the BES-T after each trial until they selected “No More Practice – I am Ready.”

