## Anticipated results

The primary goals of this study are to first establish and then confirm engagement of the negative beliefs target with the novel E2E training approach, and to also demonstrate a relationship between change in the beliefs target and therapists’ in-session delivery behaviors. Target engagement was established during the Phase 1 trial. The Phase 2 training trial will confirm target engagement by demonstrating significantly greater change in belief scores following workshop training for therapists assigned to E2E relative to the didactic group (Hypothesis 1). To test this effect, group status (E2E vs. didactic) will be entered as a predictor of post-workshop total TBES score while including a random intercept for TBES baseline score. It is anticipated that as TBES-measured belief levels approach zero, the distribution will become positively skewed. This is problematic given the goal to target and reduce belief levels as close to zero as possible. To account for the positive skew of TBES scores approaching zero, binomial-based modeling will be used to conduct a logistic regression to assess for a difference in belief reduction between those in the didactic and E2E groups following the workshop training. Figure 3 illustrates the measurement time points and pathways for testing planned hypotheses.

It is also expected that the E2E intervention will produce a specific change in negative beliefs (measured pre-and post-workshop) about exposure but not differentially affect broader beliefs about EBPs (EBPAS) in general (Hypothesis 2). Target specificity will be demonstrated by significantly greater levels of negative belief change but comparable levels of EBP belief change in the E2E group relative to didactic. The pilot nature of this study does not allow sufficient statistical power to conduct a non-inferiority test of group differences on EBPAS change, so comparison of descriptive statistics will provide initial evidence of specificity to be fully tested in a larger trial (61, 62).

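### Specificity is judged against EBPAS alone and delivery is related to beliefs alone, so the stated analyses cannot separate negative beliefs from confidence as the mechanism of E2E training

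*Protocol article*

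**What the plan says.** The Abstract states that the framework will be used to "evaluate the mechanism(s) by which training influences aspects of therapist delivery following training", and the Summary describes the procedures as isolating those mechanisms.

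- **Candidate targets.** Table 1 lists "Self-efficacy (*Candidate target" and "Knowledge (*Candidate target" at baseline, end of core didactics, end of workshop and end of study. TBES and EBPAS have the same four time points.
- **Specificity.** Under Anticipated results (Hypothesis 2), "Target specificity will be demonstrated by significantly greater levels of negative belief change but comparable levels of EBP belief change". The EBPAS comparison is descriptive, because the pilot lacks power for a formal test.
- **Target and outcome.** Hypothesis 3 models optimal and suboptimal delivery on post-training TBES. Hypothesis 4 correlates negative beliefs with exposure utilization. No other predictor is named.
- **Stopping item.** Therapist workshop measures introduces the BES-T thus: "The scale consists of six items that assess therapists’ reservations about the safety and tolerability of exposure therapy". The sixth item, which decides whether practice continues, reads "I feel very confident in my ability to deliver exposure therapy and I am committed to using it with my anxious clients". The E2E condition section states: "Therapists repeated the partner exposure task and completed the BES-T after each trial until they selected" the ready option.
- **Self-efficacy scale.** "This is a 27-item measure of therapists’ confidence in delivering exposure therapy". Every item opens with the therapist's confidence in his or her ability.

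**The concern.** The article names three constructs that training might move: negative beliefs, self-efficacy and knowledge. It then defines specificity by a fourth, general attitudes to evidence-based practice. As described, neither arm's last four hours aim at those attitudes, so similar EBPAS change in both arms says little about which of the three named constructs was responsible.

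Self-efficacy is the most plausible rival. E2E therapists practise exposure, partly in the therapist role, and didactic therapists do not. Therapists who answered that they were not yet ready all chose the therapist role for the additional rounds, and those rounds ended on a statement of confidence and commitment. The article itself reports that the self-efficacy scale predicts self-reported use of exposure, which is close to the utilization outcome of Hypothesis 4.

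If the expected results appear, the article's own criteria would credit negative beliefs. The same results would be expected if E2E built confidence and TBES moved with it. The next, larger trial could then be designed around the wrong target although data bearing on the question had been collected.

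**Working it through.** The article gives no alpha, effect size or sample-size calculation, so there is no figure to reproduce. The check asks whether the stated pattern could arise when beliefs are not the mechanism.

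**Inputs from the article**
- 36 therapists in Phase 2 (Current study; Turnover). The allocation ratio is not stated; 18 per arm is assumed.
- 21 patients recruited at the time of writing (Patient participants), so at most 21 therapists with session data.

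**Step 1. Induced association.** If only self-efficacy (SE) drives delivery, then r(TBES, delivery) = r(TBES, SE) × r(SE, delivery). With assumed values:
- −0.5 × 0.5 = −0.25
- −0.7 × 0.5 = −0.35

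In both cases the partial correlation of TBES with delivery given SE is zero.

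**Step 2. Simulation of the whole pattern.** 3,000 runs per setting, all effects assumed:
- SE = d × arm + noise
- TBES = −λ × SE + √(1 − λ²) × noise
- delivery = 0.7 × SE + √(1 − 0.49) × noise
- EBPAS = noise only
- 21 of the 36 therapists, drawn at random, have delivery data.

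Tests are two-sided at 0.05 and counted in the expected direction: a t test for TBES, a Pearson correlation for delivery, and non-significance for EBPAS. These are simple stand-ins for the planned models.

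| d | λ | TBES differs | EBPAS non-significant | TBES-delivery association | All three | TBES-delivery, adjusted for SE |
|---|---|---|---|---|---|---|
| 1.0 | 0.5 | 32.8% | 95.0% | 46.9% | 18.0% | 2.7% |
| 1.0 | 0.7 | 55.3% | 95.6% | 76.5% | 41.8% | 2.2% |
| 1.5 | 0.7 | 87.7% | 94.7% | 87.4% | 73.6% | 2.1% |

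TBES has no effect of its own in any row. The nominal one-direction error rate is 2.5%, which the adjusted model roughly keeps.

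**Step 3. How much EBPAS can show.** With 18 per arm, the 95% half-width of a standardized difference is 1.96 × √(2/18) = 0.65. Power is 32% for a 0.5 SD difference and 14% for 0.3 SD. A comparable EBPAS result is weak evidence even for that one comparator.

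**Step 4. Precision cost of adjusting.** The half-width of a correlation near zero is tanh(1.96/√(N − 3 − k)), where k is the number of covariates. With N = 21:
- k = 0: 0.43
- k = 1: 0.44
- k = 2: 0.45

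**Step 5. The reverse case.** Suppose beliefs are the only driver, with r = 0.5 with delivery and 0.7 with SE (absolute values). Then r(SE, delivery) = 0.7 × 0.5 = 0.35, and the partial correlation of beliefs with delivery given SE is (0.5 − 0.7 × 0.35)/√((1 − 0.49)(1 − 0.1225)) = 0.255/0.669 = 0.38. With N = 21 and one covariate, atanh(0.38) × √17 − 1.96 ≈ −0.30, which gives power of about 38%. Adjusted significance would miss a true belief mechanism more often than not.

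**The case against.** **The analyses may exist elsewhere.** This is a condensed article, its analysis plan is not shown and Figure 3 is not visible. Models for candidate targets are often left to a SAP. That stands as far as it goes: absence from the article does not prove that no analysis is planned. But the article does state a specificity rule, and that rule uses EBPAS alone. The point rests on the stated rule.

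**The claims are modest.** Hypothesis 2 offers initial evidence only, Hypotheses 3 and 4 are associations, and the Discussion limits the pilot to target engagement and a target-outcome relationship. This lowers the severity. It does not fit well with the Summary's wording about isolating mechanisms.

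**A reader might infer that E2E as a whole is dosed to self-efficacy.** The article does not support this. Every E2E therapist completes two self-exposure and two partner-exposure rounds whatever the answer to item 6, which governs only additional rounds. Phase 1 set the dose against a TBES benchmark, and readiness agreed with the TBES criterion in 6 of 6 therapists (4 ready and below, 2 not ready and above). That agreement shows that the two move together; it does not separate them. The article also defines negative beliefs as reluctance to use and optimally deliver exposure, so the commitment half of item 6 is not foreign to the target. Measurement considerations already discloses that the item is double-barreled and might be endorsed to end practice.

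**A reader might also infer about three hours of extra hands-on practice,** from 4 h less the 1 h review. The required timed exposures are far shorter: 2 × 5 + 2 × 8 = 26 min, or 2 × 5 + 4 × 8 = 42 min if both partner roles are timed separately. Hierarchy building and group processing take part of the rest.

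**Adjustment can mislead.** Self-efficacy may lie downstream of beliefs, so adjusting for it could remove part of a real belief effect. This stands and rules out a pass/fail rule.

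**Conclusion.** The point holds as an identification gap. As stated, specificity is tested against a measure that is not one of the article's own rival targets, and delivery and utilization are related to beliefs alone. The expected pattern would support engagement of negative beliefs and their association with delivery. It would not show that beliefs rather than confidence carried the effect. The confidence-and-commitment item adds to the overlap, but only for therapists who needed additional rounds.

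The 18% to 74% range shows that the pattern can appear readily under a confidence-only mechanism. It rests on assumed effects, 1:1 allocation and 21 therapists with session data, and it is not an estimate of the trial's error rate. Nothing here shows that beliefs are not the mechanism. Analysing the candidate targets helps but cannot settle the matter: the association with delivery is observational, E2E supervision also works on beliefs, and only therapists with enrolled patients contribute. In a disclosed pilot this is a worthwhile, cheap improvement and not a fatal flaw.

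**What to change.** In Anticipated results:

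1. Estimate the E2E-didactic difference at post-workshop for Self-efficacy and Knowledge in the same way as for TBES. Report the standardized differences for TBES, EBPAS, Self-efficacy and Knowledge side by side with confidence intervals.
2. For Hypotheses 3 and 4, report the associations of delivery and utilization with Self-efficacy and with Knowledge next to those with TBES. Add TBES adjusted for Self-efficacy as an exploratory estimate with its interval, and note that self-efficacy may be downstream of beliefs.
3. Limit the conclusion to engagement of negative beliefs and their association with delivery. Do not claim specificity or an isolated mechanism from the EBPAS comparison alone, and bring the Summary's wording into line.
4. Apply no pass/fail rule based on which contrast is larger or on whether the adjusted association is significant.

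No new assessment is needed, since all four measures are already scheduled. The cost is a few exploratory models, imprecise adjusted estimates and a mechanism claim that may come out weaker. If a separate analysis plan already contains these models, a sentence in the article saying so and the narrower conclusion would suffice.

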#### Measurement considerations

While piloting measure administration during the case-series in Phase 1 it became clear that repeatedly administering the TBES after rounds of the experiential tasks was burdensome, interrupted the learning flow, and posed a potential risk of sampling error. This led to the development of the brief BES-T measure to allow for frequent monitoring of change in the belief target without interrupting training and potentially undermining the potency of experiential learning. During the case-series analysis, therapists who endorsed feeling ready to use exposure on the BES-T go/no-go item (4 of 6 therapists) following E2E procedures also reported post-workshop TBES scores below the *a-priori* criterion score, while those who endorsed not yet feeling ready to use exposure (2 of 6 therapists) were above the TBES criterion score at post-workshop. It is possible therapists could simply endorse feeling ready to use exposure to end experiential training tasks, but the consistency between endorsement of this item with our TBES clinical criterion score would suggest therapists answered truthfully in the Phase 1 case-series. Future measurement strategies will take into closer consideration the possibility of therapists potentially endorsing a willingness to use exposure in order to discontinue experiential activities. The sixth item in the BES-T measure is also a double-barreled question assessing both therapists’ confidence and intent to use exposure that will likely need to be broken out into two separate questions in a future test of the E2E training intervention. At present, it is possible a therapist could be confident but still not intend to use exposure and the current question configuration would not allow sensitivity to this possibility. Resulting finding will be interpreted in light of this consideration. Time points for sampling therapist beliefs were carefully chosen to allow for mechanism evaluation. As depicted in Figure 3, the intervention target was assessed before, during, and after the experimental E2E training strategies were implemented. An easy to administer process measure for assessing incremental change in the belief target was also implemented during experiential E2E training tasks to measure dose response, and a rigorous micro-analytic coding system was used to quantify the outcome of interest (i.e., therapist delivery behavior; Table 1).

**Figure 3 fig3:**
[figure not shown]
Training activities, hypotheses, and measurement strategy. EBPAS = Evidence Based Practice Attitudes Scale; TBES = Therapist negative Beliefs about Exposure.

**Table 1 tab1:** Measurement strategy and timepoints.

Measure (*Objective*)	Timepoint					
	Baseline	End of core didactics	During experiential (E2E only)	End of workshop	Consult	End of study
TBES (*Primary target*)	X	X		X		X
EBPAS (*Target specificity*)	X	X		X		X
Knowledge (*Candidate target*)	X	X		X		X
Self-efficacy (*Candidate target*)	X	X		X		X
BES-T (*Target process*)			X			
Training satisfaction (*QI*)				X		X
EPCS (*Outcome*)					X	

BES-T = Beliefs about Exposure Scale – Training; EBPAS = Evidence Based Practice Attitudes Scale; EPCS = Exposure Process Coding System; Knowledge = Exposure Knowledge Measure; Self-Efficacy = Measure of Exposure Delivery Self-efficacy; TBES = Therapist negative Beliefs about Exposure; Training Satisfaction = Training Acceptability Rating Scale (TARS).

### Study procedures

#### Phase 1: Case series (complete)

Six therapists from two different clinical sites were recruited for a case-series designed to establish target engagement and determine optimal procedures for conducting the behavioral training strategies in Phase 2. During the case-series, therapists first received an 8-h didactic training on exposure therapy and the principles of its delivery to orient them to the treatment approach. Following didactics, therapists completed a series of behavioral training strategies that include both self-exposures and partner exposures. This information was used to ensure that behavioral strategies in Phase 2 of the study were appropriately dosed to engage negative beliefs, consistent with the precision implementation approach.

#### E2E design considerations

We considered a wide range of behavioral strategies with the potential to augment negative beliefs, including: delivery with confederate patients, watching exposure session videos, imaginal exposure, or exposures with the trainer in the therapist or patient role. Ultimately, we selected the two behavioral strategies (self-and partner-exposures) for this study based on preliminary support in the training literature (38, 39), our experiences with the effectiveness and tolerability of implementing these behavior strategies during training, and their face-valid match with the four main domains of therapist negative beliefs (i.e., Exposure is intolerable (1) for my patients and (2) for me; Exposure is dangerous (3) for my patients and (4) for me). We also selected these strategies based on their ability to be transportable and therefore lend to the dissemination and scalability of the training.

#### Optimizing E2E during experiential training tasks

Principles of exposure delivery for patients include: generating a fear hierarchy, selecting and titrating appropriate exposure tasks, engaging threat perceptions during exposure, tracking change in anxiety and anxious beliefs, and consolidating learning.

##### Generating a fear hierarchy

Therapists were presented with three partially complete fear hierarchies pertaining to social, contamination, and panic concerns. The goal was to represent three diverse fear domains that may elicit at least some anxiety for therapist participants. Each hierarchy consisted of seven representative exposure tasks ranging from easy (e.g., “touch snack to tabletop and eat it”) to more challenging (e.g., “touch snack to inside of garbage can and eat it”). Therapists reviewed each hierarchy and selected the one that had tasks they thought were most relevant to their own worries. Next, they added three more personally relevant exposure tasks (low, moderate, and high anxiety) to the hierarchy to practice generating unique exposure scenarios; this resulted in a personalized fear hierarchy for each participant, with a range of exposure ideas for them to choose from when initiating their first round of self-exposures. Our experience in this and in other studies suggests that all therapists have been able to identify “challenging but doable” exposure tasks using this approach and titration methods as described below.

